Given the limited resources in the “real-world” clinical environment, it is of paramount importance to establish biomarkers that can help predict which patient will benefit from specific therapies and thus to tailor rehabilitation. We will explore whether baseline WM- $\mu$ S integrity (HP3.3) and aptitude to achieve bimanual MskL on a rehabilitation robot (REApian®, AXINESIS) (HP3.4) predict functional gains induced by the intensive HABIT-ILE therapy. Furthermore, the predictive model could be refined by combining the three aspects (clinical assessments, imaging and robotics).

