## METHODS AND STUDY DESIGN

In order to compare HABIT-ILE with the recovery of motor control during a time equivalent control period involving standard activity and conventional rehabilitation, we will run a single-blind randomized clinical trial (RCT) similar to Grand Challenge 2 with a parallel, cross-over group design (see Figure 5). The stroke patients will be randomly assigned either to a HABIT-ILE therapy for 10 days (5 days a week, 5 hours per day during 2 weeks; total = 50 hours) or to the time-equivalent control period with a minimization software to stratify patients for plegia/paresis/no motor deficit, gender, age, stroke in the (non-)dominant hemisphere, etc. The control group will follow its usual rehabilitation care and document all activities and therapeutic interventions during the initial 2-week period. A complete assessment will be performed for both groups before (T0) and after (T0+15d) the intervention/control period as well as 3 months post-intervention (T0+90d). An additional assessment will be added for the control group at the end of their delayed HABIT-ILE intervention, allowing us to collect data reflective of the effect of HABIT-ILE from a larger group. Each assessment will comprise clinical assessments, robotic measurements and neuroimaging data including multi-shell HARDI DW-MRI to be analyzed using ICTEAM frameworks for the extraction of WM  $\mu$ S indices.

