## GRAND CHALLENGE 4: EXPLORING MECHANISMS OF TRAINING-INDUCED FUNCTIONAL RECOVERY THROUGH WM MICROSTRUCTURE IN VERY EARLY LESIONS VS ADULT ACQUIRED LESIONS

The identical experimental settings of WP 2 and 3 make it possible to directly compare WM baseline damage and training-induced changes between hemiplegic CP infants and adult stroke patients, both at the macroscopic level using whole-brain tractography and at the microscopic level using voxel-wise, model-based microstructural features. The deep underpinning of the differential repair mechanisms based on the initial conditions and age of the patients is likely to bring neurophysiological responses to the conditions allowing WM repair or training-induced changes. Investigating the best responders depending on initial conditions should help to better tailor treatment to each patient.

### RESEARCH HYPOTHESES OF GRAND CHALLENGE 4

Grand Challenge 4 will test the following hypotheses:

1. Experience-induced remodeling of the damaged CST occurs both in CP infants and adult stroke patients undergoing HABIT-ILE, but is stronger in developing CP infants **(HP4.1)**;
2. Neuroinflammation quantified by DW-MRI biomarkers is more predominant in developing CP infants compared to chronic adult stroke patients **(HP4.2)**.  
In both adult stroke patients and CP infants,
3. response to HABIT-ILE correlates *positively* with baseline DW-MRI markers quantifying the residual integrity of the damaged CST **(HP4.3)**;
4. response to HABIT-ILE correlates *negatively* with baseline DW-MRI markers quantifying a baseline enhancement of the ipsilateral, uncrossed CST **(HP4.4)**;
5. Combining DW-MRI  $\mu S$  markers of the CST with a whole-brain index of WM  $\mu S$  integrity correlates more closely with clinical response to HABIT-ILE than using exclusively the DW-MRI markers of the CST **(HP4.5)**.

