adult stroke patients (**HP4.2**). Indeed, a recent study in children with unilateral CP demonstrated that in contrast to typically developing children, children with unilateral CP do not present a maturational process of increasing CST integrity (Papadelis et al., 2019). The authors of this study also reported a decreased FA in both CSTs of children with unilateral CP. They attributed the absence of increase with age to a possible perinatal disruption of CST myelination and axonal integrity, due to persisting neuroinflammation during development. Stroke triggers a robust inflammatory response and, through multiple mechanisms such as glial activation, global brain inflammation might persistently shape the pathophysiology of brain injury after a stroke and promote decline of global brain functions like cognition, affecting the patients' long-term neurological outcome (Shi et al., 2019). Thus, in adults with stroke, neuroinflammation is major during the early (sub)acute phase of stroke and plays a key role in neuroplasticity (that could be both positive and/or deleterious) and, whereas neuroinflammation has been observed to decrease afterwards, it could persist in chronic stroke (Jayaraj et al., 2019; Shi et al., 2019; Thomas Carmichael, 2016).

Third, in an attempt to develop DW-MRI biomarkers common to CP infants and adult stroke patients, we will explore whether response to HABIT-ILE correlates *positively* with baseline DW-MRI markers quantifying the residual integrity of the damaged CST (**HP4.3**). We will determine which common level of residual integrity of the damaged CST predicts the larger functional gains after HABIT-ILE intensive therapy, and whether some threshold of damage limits response to HABIT-ILE. Potentially, based on ICTEAM algorithms, it would be possible to stratify the CP and stroke subjects in "good responders", "poor responders" and "intermediate responders" and to extract baseline DW-MRI markers quantifying the residual integrity of the damaged CST for each subgroup. Alternatively, if CST integrity thresholds common to CP infants and adult stroke patients cannot be established, this would suggest again a different neuroplastic potential in the developing and aged brain.

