Fourth, we hypothesize that response to HABIT-ILE correlates *negatively* with baseline DW-MRI markers quantifying a baseline enhancement of the ipsilateral, uncrossed CST (**HP4.4**), to a larger extent in CP infants than in adult stroke patients. The same procedures as for hypothesis **HP4.3** will be applied focusing on a negative correlation with the ipsilateral, uncrossed CST, expected to be stronger in CP infants. Indeed, it is expected to play a minor role, if any, in the damaged brain of adult primates (Zaaimi et al., 2012). In contrast, following early brain damage in CP, direct uncrossed axons can be preserved between the injured hemicortex and the more affected hemibody, which can thus be controlled by both sides of the brain [73]. The ipsilateral CST can therefore convey part of or all information for controlling the paretic hemibody (Guzzetta et al., 2007b). Studying carefully the relation between ipsilateral CST and response to HABIT-ILE will help further understand the mechanisms of recovery depending on initial condition, and *in fine* help fine-tune rehabilitation content regarding the initial role of the ipsilateral hemicortex and CST.

Fifth, combining DW-MRI markers of the CST with a whole-brain index of WM  $\mu S$  integrity may better predict the clinical response to HABIT-ILE than using the CST-specific markers alone (**HP4.5**). Multiple regression models will be tested to establish correlations between the clinical response to HABIT-ILE and  $\mu S$  indices of (1) the CST, (2) the corpus callosum and (3) whole-brain indices of WM  $\mu S$  integrity. Indeed, whereas a minimal level of CST integrity is undoubtedly needed to allow meaningful recovery, it becomes clear that cognitive components also play a key role in motor function recovery, at least in adult stroke patients (Rinne et al., 2018b). Exploring WM  $\mu S$  integrity beyond the CST may thus help in refining the stratification of patients in "good responders", "poor responders" and "intermediate responders".

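### The baseline MRI markers are tied to gains after HABIT-ILE with no control contrast, so the stated analysis cannot tell a marker of benefit from a marker of general course

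*Protocol*

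**What the plan says.** **Purpose.** Under the research hypotheses of Grand Challenge 3, the protocol calls it very important to "establish biomarkers that can help predict which patient will benefit from specific therapies and thus to tailor rehabilitation". Grand Challenge 4 likewise wants to study the best responders in order to tailor treatment.

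**Analysis.** Grand Challenge 4 states HP4.3 and HP4.4 as correlations between baseline DW-MRI markers and response to HABIT-ILE. For HP4.3 it adds: "We will determine which common level of residual integrity of the damaged CST predicts the larger functional gains after HABIT-ILE intensive therapy". It will also look at "whether some threshold of damage limits response to HABIT-ILE", and it raises the possibility of sorting subjects into good, intermediate and poor responders. HP4.4 is to follow the same procedures. HP2.3 (infants) and HP3.3 (adults) have functional gains predicted by baseline white-matter integrity; the Grand Challenge 3 text describes HP3.3 as predicting gains brought about by HABIT-ILE. None of these places names a control contrast for the marker.

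**Controls.** Both trials randomise 24 per arm to HABIT-ILE or a usual-activity period. Controls are assessed at T0, T0+15 and T0+90, before their delayed HABIT-ILE. For the adult trial, the assessment after that delayed course is described as "allowing us to collect data reflective of the effect of HABIT-ILE from a larger group".

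**HP4.5.** The hypothesis is that CST markers combined with a whole-brain index of white-matter "integrity correlates more closely with clinical response to HABIT-ILE than using exclusively the DW-MRI markers of the CST". The method given is: "Multiple regression models will be tested to establish correlations between the clinical response to HABIT-ILE and" indices of the CST, the corpus callosum and the whole brain.

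**The concern.** Whether a marker predicts benefit is a question about the difference between arms: does the effect of HABIT-ILE over usual activity change with the marker? The gain of a treated participant is the sum of the treatment effect and whatever would have happened anyway. A marker related only to the second part correlates with the gain just as well.

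The risk is greatest in two places. Infants of 6 to 18 months keep developing up to T0+90, and baseline CST integrity may forecast that development. Data from the controls' delayed HABIT-ILE have no concurrent control at all.

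At stake is the clinical use of the result. A damage threshold or responder class drawn from treated participants alone could be used to decide who is offered intensive therapy, although it may only identify those who do well under either regimen.

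**Working it through.** **1. The plan's own figures.** The only sample sizes stated are for the between-group clinical comparison: 15 per group in infants and 16 in adults, alpha 0.05, power 0.90. Sidedness is not stated; two-sided is assumed because it reproduces them. With n = 2(1.960 + 1.282)² × (SD/difference)²:

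- Infants: 21.01 × (5.9/7.2)² = 14.1, so 15; t-test version 15.1.
- Adults: 21.01 × (5/6)² = 14.6, so 15; t-test version 15.6, so 16.

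Both are reproduced to within one participant. Neither covers a marker analysis.

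**2. Inputs for the marker check.** From the protocol: 15 to 24 analysable per arm. The upper end is the number included. The stated MRI success of at least 70% in infants gives 0.7 × 24 = 16.8, inside that range. The treatment effect is 1.2 SD (6/5 = 1.20; 7.2/5.9 = 1.22). Assumed, because the protocol gives no value: a marker slope of 0.5 SD.

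Model: gain = 1.2 × arm + slope × marker + error, with error variance 0.75, simulated 6,000 times per case. In an arm with slope 0.5 the total variance is 0.25 + 0.75 = 1, so r = 0.5.

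| True state | n per arm | Treated arm: significant positive correlation | Mean r, treated / control | Marker-by-arm test significant |
|---|---|---|---|---|
| Same slope in both arms (prognostic only) | 15 | 49% | 0.48 / 0.49 | 4.5% |
| Same slope in both arms (prognostic only) | 24 | 72% | 0.49 / 0.49 | 4.9% |
| Slope 0.5 treated, 0 control (true marker of benefit) | 15 | 50% | 0.49 / 0.00 | 29% |
| Slope 0.5 treated, 0 control (true marker of benefit) | 24 | 74% | 0.49 / −0.01 | 47% |

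The treated-arm column is nearly the same in both states (49% against 50%, 72% against 74%). That analysis carries no information on which state is true.

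**3. Hand check and range.** The treated-arm figures are simply the power of a correlation test, Φ(atanh(r) × √(n − 3) − 1.96). For r = 0.5, n = 24: 0.549 × 4.583 = 2.52, and Φ(0.56) = 71%. For n = 15: 0.549 × 3.464 = 1.90, and Φ(−0.06) = 48%. Over r = 0.3, 0.5 and 0.7 the formula gives 19%, 48% and 85% at n = 15, and 29%, 71% and 98% at n = 24.

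**4. HP4.5.** The two predictor sets are nested. One pure-noise index was added to a CST marker with an assumed r of 0.4 (3,000 runs).

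| Criterion | n = 24 | n = 48 |
|---|---|---|
| Mean in-sample multiple R, CST only to combined | 0.41 to 0.45 | 0.39 to 0.42 |
| Noise index wins by in-sample R² | 100% | 100% |
| Wins by adjusted R² | 34% | 33% |
| Wins by leave-one-out error | 18% | 18% |
| Wins by nested F-test at 0.05 | 5.7% | 4.6% |

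The expected in-sample rise in R² is about (1 − R²)/(n − 2). At n = 24 this is (1 − 0.192)/22 = 0.037 (simulated 0.038); at n = 48, (1 − 0.171)/46 = 0.018 (simulated 0.018).

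**The case against.** **The aims are exploratory.** The protocol says so of the step combining the two populations, and it uses the language of exploring for HP3.3 and HP4.3. Responder classes are only a possibility, and no primary clinical comparison is affected. This stands, and it limits the weight of the point. It does not turn a prognostic association into evidence of benefit.

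**A control contrast is implied.** HP3.3 sits under a stem that compares HABIT-ILE with conventional rehabilitation, the protocol calls the between-group comparison crucial, and the generalized linear models are not restricted to treated participants. This stands in part. But those models relate microstructure to motor skill learning and name no marker-by-arm term, and the detailed text for HP4.3 and HP4.4 speaks only of gains after, or response to, HABIT-ILE.

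**Untreated change may be small.** Adults are more than six months after stroke, and pilot children did not improve over a two-week control phase. This weakens the concern at T0+15. It does not settle T0+90 in infants, and the pilot was 10 children aged 12 to 40 months.

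**The sizes are assumed.** Correct: no marker correlation is given in the protocol. The percentages in the treated arm are the power of a correlation test at the chosen r, not error rates of this trial.

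**Delayed-treatment data.** The sentence on the larger group does not mention markers. Their use in the marker analyses is possible, not stated.

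**A stronger reading of HP4.5.** A reader might infer that HP4.5 is bound to come out true, because adding predictors never lowers the in-sample multiple correlation. The protocol does not fix that criterion: it says the combination may predict better and that models will be tested. Under a nested F-test a noise index wins only about 5% of the time, and the choice of metric and any cross-validation may properly be left to the SAP.

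**Conclusion.** The point holds for HP4.3 and HP4.4, and for HP2.3 and HP3.3 as described: the stated purpose is to predict benefit, and the stated analysis can show only association with gain among treated participants. Under an assumed common slope of 0.5 SD, a purely prognostic marker would pass that analysis in about 49% to 72% of trials with 15 to 24 per arm, against about 5% for the marker-by-arm test. These figures are illustrative and move with the assumed slope.

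A reader might go further and infer that the project cannot show who benefits. That is true of the analysis as written but not of the design, since each trial has randomised controls with the needed assessments. HP4.5 leaves only a request to state its criterion.

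**What to change.** - **HP2.3, HP3.3, HP4.3, HP4.4.** Within each trial, model the change in the clinical outcome from T0 to T0+15 and from T0 to T0+90 on arm, baseline marker and marker-by-arm, using both randomised arms. Rest any claim that a marker predicts benefit, and any responder threshold or class, on the interaction with its confidence interval. Otherwise call the marker prognostic.
- **Delayed HABIT-ILE in controls.** If these data enter a marker analysis, report it separately as uncontrolled and do not use it to support a claim about benefit.
- **HP4.5 (minor).** Compare the CST-only and combined models by a nested F-test or a cross-validated criterion, with any selection of indices done inside the folds.

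**Cost.** A change of analysis wording; no new visits, scans or participants. The downside is power: about 29% at 15 per arm and 47% at 24 per arm for an assumed slope of 0.5 against 0. A null interaction would not rule out a marker of benefit, and these results should stay labelled exploratory.

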## STATISTICAL ANALYSIS

No DTI pre-post intervention analyses in infants have been published so far. However, since CST integrity measured with DTI is highly correlated with manual ability (Bleyenheuft et al., 2007), we performed a sample size calculation based on the AHA score of the pilot study performed in 10 infants with unilateral CP (see “pilot data”). A mean improvement of 8,2 AHA units (standard deviation=5.9 AHA units) after the intensive therapy was reported. Thus, our hypothesis is an incremental improvement of 1 SD between the HABIT-ILE group and the control group (between group difference =7,2, SD=5,9). With  $\alpha=0.05$  and a  $1-\beta=0.9$ , a sample size of **15 participants per group is required**. Considering potential drop-outs and data loss in MRI, **24 participants will be included in each group**. Neuroplastic changes and secondary outcomes will be compared between groups using analysis of variance (ANOVA). Non-parametric methods will be performed whenever ANOVA assumptions are not met. Time-onset influence will be tested at the 4th assessment using an ANOVA.

Separate generalized linear models (GLM) will be estimated for the CST and whole-brain WM (ICTEAM models) to infer the correlations between  $\mu S$  integrity at baseline/after intervention and the MskL outcomes (bimanual SAT). Finally, an overall GLM will be estimated to combine CST and whole-brain  $\mu S$  integrity. The *R* software will also be used for bimanual MskL curves modelling.

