In a breakthrough exploratory step, we will try to combine functional and imaging data of CP infants and adult stroke patients using advanced model programming. Recovery in CP infants and stroke adults will be summarized and a normalization of the imaging data will be attempted for comparison in a common template. Whole-brain mapping of the two populations onto a common space may turn out to be too arduous due to very different brain sizes and large deformities in infants with CP. In that case, DW-MRI markers can always be compared after an adequate averaging over segmented sub-regions of the WM, such as the damaged or undamaged CST or regions not directly related to motor functions. Segmentation of the WM in the adult brain has become a routine task supported by many open-source software platforms. Improvements in the segmentation of the infant brain have also been gradually added to that existing software as well.

First, we hypothesize that, compared to baseline, HABIT-ILE intensive therapy induces remodeling of the  $\mu S$  indices of the damaged CST both in CP infants and adult stroke patients, but more so in developing CP infants **(HP4.1)**. The advantage of those DW-MRI indices is that their scale does not depend on brain size, brain age and are in theory only related to the morphology of the white matter independent of the imaging voxel size. If the hypothesis is verified (larger remodeling of the  $\mu S$  indexes in CP infants than in adult stroke patients), this would confirm potentially larger neuroplastic changes in the developing brain than in the aged brain, especially when combined with intensive rehabilitation, allowing for a lifespan quantification of neuroplastic potential. If the hypothesis is not verified, this would challenge the “classic” theory of larger neuroplastic potential in the developing brain.

Second, along the same line, we hypothesize that neuroinflammation quantified by DW-MRI biomarkers such as DIAMOND’s extra-axonal restricted diffusivity is more persistent in developing CP infants than in chronic

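### HP4.3 reads failure to find a corticospinal-tract (CST) integrity threshold common to infants and adults as a sign of different neuroplastic potential, with no test of that difference

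*Protocol*

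**What the plan says.** The Grand Challenge 4 section lists HP4.3 among the hypotheses to be tested: in both populations, response to HABIT-ILE correlates positively with baseline diffusion-MRI markers of residual CST integrity. The text on HP4.3 adds that the investigators will look for a common level of integrity that predicts larger gains, and for "whether some threshold of damage limits response to HABIT-ILE". It also says that potentially "it would be possible to stratify the CP and stroke subjects in" good, poor and intermediate responders.

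It then interprets a negative result: "if CST integrity thresholds common to CP infants and adult stroke patients cannot be established", then "this would suggest again a different neuroplastic potential in the developing and aged brain". It gives no criterion for when a threshold counts as not established, and no comparison of thresholds or of integrity–gain relations between the populations.

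The same section introduces the pooled work as exploratory: "In a breakthrough exploratory step, we will try to combine functional and imaging data". For HP4.1 (remodeling of the damaged CST is stronger in infants than in adults), it says: "If the hypothesis is not verified, this would challenge the" classic theory that the developing brain has the larger plastic potential.

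Both trials are sized only for the between-arm difference in the Assisting Hand Assessment (AHA). For infants this is "between group difference =7,2, SD=5,9", from which "15 participants per group is required". For adults it is a difference of 6 with SD 5, from which 16 per group. Each trial enrols 24 per group.

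**The concern.** A search that finds no common threshold is compatible with at least three situations: the populations differ, they share a threshold that the data are too imprecise to locate, or no sharp threshold exists in either. The protocol names only the first.

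The protocol itself lists non-biological reasons why the search could fail:
- Large lesions may defeat segmentation and tract clustering in infants (section on project risks).
- Mapping infants and adults to a common space may prove too difficult (Grand Challenge 4).
- Repeated unsedated MRI is expected to succeed in at least 70% of infants (section on project risks).
- Whether voxel size will be the same in both studies is undecided (HP1.4).

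None of these is carried into the interpretation of HP4.3. Comparing the developing with the mature brain is the purpose of Grand Challenge 4, so a difference suggested by imprecision alone would bear on its main message. This is an interpretation fixed in the protocol text, not a detail left to a later analysis plan.

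**Working it through.** **1. The plan's own figure.** Sample size per group for two means, two-sided 0.05, power 0.90: n = 2 × (1.960 + 1.282)² × (SD/difference)².
- Infants: 2 × 10.51 × (5.9/7.2)² = 14.1, so 15. The t-based value is 15.1, so 16. The plan states 15.
- Adults: 2 × 10.51 × (5/6)² = 14.6, so 15. The t-based value is 15.6, so 16. The plan states 16.

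Both figures reproduce to within one patient. They concern the arm comparison. No power or precision is stated for HP4.3.

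**2. Analysable numbers for HP4.3.**
- Immediate HABIT-ILE arms: 24 infants and 24 adults.
- Immediate arms with 70% usable infant MRI: 24 × 0.7 = 16.8, taken as 16, and 24 adults.
- Delayed-treatment controls pooled, 70% usable infant MRI: 48 × 0.7 = 33.6, taken as 33, and 48 adults.
- Delayed-treatment controls pooled, no MRI loss: 48 and 48.

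**3. Assumptions.** The protocol gives no correlation between baseline integrity and response, so r is varied from 0.3 to 0.7 and set equal in the two populations. It gives no criterion for established either. The proxy is a significant correlation in both populations, two-sided 0.05.

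**4. Formula.** Power in one population is Φ(atanh(r) × √(n − 3) − 1.960). Chance of failure is 1 − (infant power × adult power).

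Example, r = 0.5 with 24 and 24: atanh(0.5) = 0.549; 0.549 × √21 = 2.517; 2.517 − 1.960 = 0.557; Φ = 0.711. Joint success is 0.711² = 0.506, so failure is 49%.

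**5. Chance of failure when the populations are identical.**

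| Infants / adults | r=0.3 | r=0.4 | r=0.5 | r=0.6 | r=0.7 |
|---|---|---|---|---|---|
| 16 / 24 | 94% | 84% | 64% | 37% | 14% |
| 24 / 24 | 91% | 76% | 49% | 21% | 4% |
| 33 / 48 | 78% | 48% | 18% | 4% | 0% |
| 48 / 48 | 70% | 34% | 8% | 1% | 0% |

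One-sided testing, which the directional hypothesis would allow, gives 83%, 62%, 35%, 12% and 2% at 24/24.

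**6. A check on thresholds themselves.** Two identical populations were simulated (6,000 runs per setting) and the distance between their estimated cut-offs recorded. The table shows the share of runs in which the cut-offs differ by more than 0.5 marker SD.

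| True relation and cut-off method | Infants / adults | r=0.3 | r=0.5 | r=0.7 |
|---|---|---|---|---|
| Linear; Youden cut-off for response above the median | 24 / 24 | 58% | 48% | 36% |
| Linear; Youden cut-off for response above the median | 33 / 48 | 54% | 42% | 30% |
| Sharp step; one-step change-point | 24 / 24 | 51% | 18% | 1% |
| Sharp step; one-step change-point | 33 / 48 | 43% | 8% | 0% |

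Without a sharp step, estimated cut-offs from identical populations often disagree. With a real step and a strong association, they rarely do.

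**The case against.** **It is one hedged sentence in an exploratory aim.** The wording is conditional, the pooled analysis is labelled exploratory, and neither trial's primary outcome depends on it. A reader might infer that the protocol commits itself to claiming a difference. It does not: it says a failure would suggest one. That lowers the weight of the point. It does not repair the logic, because an exploratory null result is still not evidence of a difference.

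**The percentages rest on an invented criterion.** This stands. A significant correlation is not a threshold, and the proxy also counts runs in which both populations are null. Discordant results (one significant, one not), the pattern most naturally read as a difference, occur less often. At 24/24 and r = 0.5 the rate is 2 × 0.711 × 0.289 = 41% rather than 49%. At r = 0.4 it is 2 × 0.493 × 0.507 = 50% rather than 76%. The figures should not be quoted as rates of false claims.

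**Failure is not shown to be likely.** A reader might infer that failure is likely at this sample size whatever the truth. The documents do not support that. Controls in both trials are offered or given HABIT-ILE later, and the Grand Challenge 3 design section says this provides data on its effect from a larger group. With those controls pooled, failure is 18% at r = 0.5 and 4% at r = 0.6. The 70% MRI figure is also a floor.

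**HP4.1 is a different case.** A reader might take HP4.1 as a second instance of low power producing a claim of difference. It runs the other way: there a null is read against an infant advantage, and HP4.1 is itself a between-population comparison. Its only flaw is that non-verification counts as contrary evidence with no precision condition.

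**A slope interaction alone would not answer a threshold question.** This also stands. Equal slopes can coexist with different thresholds, so the fix covers both.

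**Conclusion.** The point holds as a defect of inference. HP4.3 treats failure to establish a common threshold as suggesting a population difference, attaches no test of that difference, and allows for none of the technical causes of failure the protocol lists elsewhere. This conclusion needs no figure.

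Its size cannot be fixed from the documents. Under the assumed proxy and a common r, failure with identical populations runs from about 91% (r = 0.3) to 4% (r = 0.7) with 24 per population. With delayed-treatment controls pooled and 70% infant MRI success, it runs from about 78% to 0%. The problem is serious for weak to moderate associations and small for strong ones, or for a sharp true threshold with a strong association.

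HP4.1 needs only a related precision condition. Neither trial's primary comparison is affected.

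**What to change.** Replace the HP4.3 sentence with text to this effect:

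> A difference between infants and adults will be suggested only by a direct between-population comparison in a joint model: the population-by-baseline-CST-integrity interaction and, where thresholds are estimated, the difference between the two thresholds, each reported with its 95% CI. If these intervals do not exclude equality, failure to find a common threshold will be reported as inconclusive.

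Gain is scored with the mini-AHA in infants and the ad-AHA in adults, so the text should also state the scale on which gain enters the joint model.

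For HP4.1, say that non-verification challenges the classic theory only if the CI for the infant–adult difference in remodeling excludes a relevant infant advantage, with the size regarded as relevant stated beforehand.

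The cost is wording and a joint model on data already planned, with no extra patients or scans. The small downside is that these exploratory comparisons will often be inconclusive.
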